## Abstract

**Background:**

Poor response to ovarian stimulation with exogenous gonadotrophins occurs in 9–24% of women undergoing in vitro fertilisation (IVF) treatment, which represents an estimated 4000–10,000 women per year in the UK. Poor responders often have their treatment cycle cancelled because of expected poor outcome.

One treatment strategy that may influence outcome is the choice of pituitary suppression regimen prior to the initiation of ovarian stimulation. The three commonly used pituitary suppression regimens in IVF treatment are:

(1) the GnRH agonist *long *regimen,

(2) the GnRH agonist *short *regimen and

(3) the GnRH *antagonist *regimen.

A systematic review of randomised controlled trials of these pituitary suppression regimens has shown the evidence to be either inconclusive or inconsistent. We therefore designed a three arm randomised trial to evaluate the effectiveness of these regimens in women who had poor ovarian response in a previous IVF treatment cycle.

**Methods/design:**

Consenting, eligible women will be randomised to one of the three regimens using an internet-based trial management programme that ensures allocation concealment and employs block randomisation and minimisation for prognostic variables. The primary outcome is the number of oocytes retrieved. Other outcomes include total dose of follicle stimulating hormone (FSH) used for ovarian stimulation, *mature *oocytes retrieved, embryos available for transfer, implantation rate and clinical pregnancy rate.

The sample size for this trial has been estimated as 102 participants with 34 participants in each of the three arms. Appropriate interim analysis will be conducted by a Data Monitoring and Ethics Committee (DMEC), and the final analysis will be by intention to treat.

**Trial registration:**

ISRCTN27044628

## Background

Poor ovarian response, defined as failure of the development of sufficient number of mature follicles to proceed to oocyte retrieval or yielding only a few oocytes following gonadotrophin stimulation in women undergoing in vitro fertilisation (IVF) treatment, occurs in 9–24% of women [1]. Poor ovarian response is likely to be an increasing problem with women delaying childbearing and presenting for treatment later in their reproductive life. In comparison to normal responders these patients have impaired fertilisation rates, lower embryo quality and decreased pregnancy rates [2]. Poor responders often have their treatment cycle cancelled because of expected poor outcome [3]. This causes emotional distress for the couple, as well as a financial burden on the couple or the service provider.

Treatment of poor responders who are undergoing IVF treatment remains a challenge. Various treatment regimens and interventions have been proposed in an effort to improve ovarian response and IVF outcome in this group of patients. These include different regimens for pituitary suppression, controlled ovarian hyperstimulation (COH) as well as adjuvant therapies [4]. Currently, the choice of pituitary suppression regimens proposed for the management of poor responders is mainly based on individual centre's or clinician's preferences, with no single protocol considered to be superior over the other. Of the various available pituitary suppression regimens, the three commonly used ones are:

(1) the GnRH agonist long regimen,

(2) the GnRH agonist short regimen and

(3) the GnRH antagonist regimen.

To address the question of their effectiveness, we performed a systematic review and meta-analysis. Literature searches were conducted in MEDLINE, EMBASE, the Cochrane Database, National Research Register and ISI proceedings to identify randomised trials comparing the effects of the above three regimens. We identified seven randomised controlled trials comparing the regimens with each other.[5-11] There were no trials that compared all three regimens against each other. The quality of these 7 randomised trials was generally poor (only 2/7 trials had adequate allocation concealment reported). These trials were also generally small, leading to imprecision in their findings, even when combined in a meta-analysis (Figure 1). Furthermore, there was substantial clinical and statistical heterogeneity amongst the trials. The findings were inconclusive or inconsistent (Figure 1). A well designed, adequately powered, three arm trial comparing the long GnRH agonist regime versus the short GnRH agonist regime versus the GnRH antagonist regime is therefore needed.

**Figure 1 F1:**
[figure not shown]
Meta-analysis of the number of oocytes retrieved with different pituitary suppression regimens in poor responders.

## Methods/design

### Objective

In the proposed trial we will evaluate which of the three commonly used down regulation regimens is the most effective for women who have shown poor response in their previous IVF treatment cycle.

### Design

A prospective, allocation concealed, assessor-blind, three-arm randomised-controlled-trial.

### Primary endpoints

• Number of eggs retrieved per IVF treatment cycle started.

### Secondary endpoints

• The total dose of follicle stimulating hormone (FSH) used for ovarian stimulation

• The number of mature eggs retrieved

• The number of embryos available for transfer

• The clinical pregnancy rate and

• The embryo implantation rate

### Inclusion Criteria

Any woman undergoing an IVF treatment cycle who fits the criteria to be a "poor responder" is eligible to participate in the trial.

For this study a "poor responder" is defined as a woman who had a previous IVF treatment cycle in which she was stimulated with a daily dose of FSH of 300 IU or more and

• Produced an inadequate number of mature follicles (three or less follicles measuring > 17 mm) following stimulation for at least nine days; OR

• Had three or less oocytes retrieved at oocyte retrieval.

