### Randomisation

Third party, distant, internet-based block randomisation with minimisation will be used to ensure randomisation and complete allocation concealment. The aim of minimisation would be to balance for the following prognostic variables (age, body mass index, previous pregnancies and previous live birth). Women may be randomised into the study by internet randomisation [12] or by telephoning a central office.

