### Trial statistics

#### Number of participants

Sample size calculation was based on the observed differences in eggs collected from existing literature as well as on the judgement on what constitutes as a clinically Minimally Important Difference (MID), which was judged to be increasing the number of oocytes retrieved from 3 to 5. For this difference of 2 oocytes retrieved, with a standard deviation of 2.5 (as observed in the existing literature), for a power of 90% and an alpha of 5%, 102 women in total will need to be recruited (34 each of the three arms of the trial).

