#### Step 1: Summarising trial data

Baseline data and outcome data will be summarised separately. For continuous variables (eg age and FSH level), we will examine the distribution of the observations, and if normally distributed we will then summarise them as means with standard deviations (SDs). If they are non-normally distributed, then medians and inter-quartile ranges (IRQs) will be reported. For dichotomous data (eg clinical pregnancy), we will provide proportions (or percentages).

For our main outcome measure (the number of oocytes collected), as the number of oocytes is not a dichotomous or continuous variable but is a count, and as it is more likely not to be normally distributed, a model for count such as the negative binomial model will be used for analysis.

In addition to the baseline and outcome data, we will also summarise the recruitment numbers, those participants lost to follow-up, protocol violations and other relevant data.

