#### Step 4: Adjustments and sensitivity analyses

If randomisation fails to achieve balanced groups, then we will perform secondary analyses in which we will adjust for unbalanced prognostic factors using procedures such as logistic regression. If the primary unadjusted analysis and secondary adjusted analysis are at discordance, then we will give greater weighting to the primary analysis in the interpretation of trial findings.

For issues such losses to follow-up, missing data, and protocol violations, we will attempt sensitivity analyses to explore the effect of these factors on the trial findings. As a secondary analysis, we will adjust for missing data using imputation techniques to explore the effects of such imputations on the trial findings.

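### The primary comparison is fixed as unadjusted, so previous-cycle response, which must be classified for every woman at entry, is not used to sharpen it: a small, avoidable loss of precision

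*Protocol article*

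**What the plan says.** Under Inclusion Criteria, the protocol article defines a poor responder by an earlier cycle at 300 IU FSH or more daily in which the woman met one of two conditions. The follicle route is worded "Produced an inadequate number of mature follicles (three or less follicles measuring > 17 mm) following stimulation for at least nine days; OR". The alternative, by oocyte count, is worded "Had three or less oocytes retrieved at oocyte retrieval". No woman can be randomised until that earlier response has been classified.

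The primary endpoint is "Number of eggs retrieved per IVF treatment cycle started". Under Randomisation, minimisation is to "balance for the following prognostic variables (age, body mass index, previous pregnancies and previous live birth"). Previous-cycle response is not on that list.

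Step 1 of the statistical analysis proposes a count model, such as the negative binomial, for the primary outcome and names no covariates. Step 2 lists ANOVA or Kruskal-Wallis followed by pairwise tests, again without covariates. Step 4 allows adjustment only if randomisation leaves the groups unbalanced, and only as a secondary analysis. It then ranks the two: "If the primary unadjusted analysis and secondary adjusted analysis are at discordance, then we will give greater weighting to the primary analysis".

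FSH level appears once in the analysis text, as an example: "For continuous variables (eg age and FSH level), we will examine the distribution of the observations".

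**The concern.** How a woman's ovaries responded to stimulation last time is an obvious candidate predictor of how many oocytes she yields this time. Here the information is in hand before randomisation, because eligibility depends on it. It is neither balanced by minimisation nor used in the primary comparison, so whatever outcome variation it explains stays in the error term.

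Precision is at stake, not validity. Step 2 says that the emphasis will be on 95% confidence intervals, and these are wider than they need be. The 34 per arm is also sized for a single two-arm test at 5% with no stated allowance for dropout, whereas Step 2 requires multiplicity-adjusted pairs, for which power is already lower. Finally, if prior response happens to be unbalanced in arms of 34, Step 4 still prefers the unadjusted result.

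This is a choice that the article states. It is not a detail left to an analysis plan, since a plan faithful to Step 4 could not make an adjusted analysis primary.

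**Working it through.** **Inputs from Number of participants.** The difference is 2 oocytes ("increasing the number of oocytes retrieved from 3 to 5"). The SD is 2.5 ("with a standard deviation of 2.5 (as observed in the existing literature")), and nothing describes it as a residual SD after adjustment. Power is 90%, alpha 5%, with 34 per arm. I assume a two-sided test, no dropout, and a normal approximation to the count outcome.

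**1. The plan's own figure.** Normal formula: n = 2(1.960 + 1.282)² × 2.5² / 2² = 32.8, so 33 per arm. With the noncentral t, power is 89.3% at 33 and 90.2% at 34 per arm, so 34 is needed. The stated 34 per arm (102 in total) therefore reproduces as an unadjusted two-group calculation.

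**2. Precision without adjustment.** The standard error of a pairwise difference is 2.5 × √(2/34) = 0.606. With t(66) = 1.997, the 95% interval half-width is 1.997 × 0.606 = 1.21 oocytes. At the Bonferroni level 0.05/3, power for one pair is 79.7%.

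**3. Effect of a baseline covariate.** If the covariate has correlation r with the outcome, the residual SD is 2.5 × √(1 − r²), and the variance falls by the fraction r².

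**4. What r is plausible.** The documents give none. Entry by the oocyte route limits the earlier count to 0–3, which weakens any correlation. In an illustrative simulation (negative binomial counts, mean 4 to 6, SD 2.5 to 4, kept only if the earlier count was 3 or fewer), nominal between-cycle correlations shrank as follows:

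| Before restriction | After restriction |
|---|---|
| about 0.3 | 0.14–0.16 |
| about 0.5 | 0.25–0.29 |
| about 0.7 | 0.38–0.44 |

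Other illustrative simulations with the same truncation gave 0.17–0.30 (from 0.38–0.69) and about 0.23–0.32 (from 0.50–0.71). I take 0.15 to 0.3 as the working range.

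**5. Results at 34 per arm, difference 2 (noncentral t, 66 df).**

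| r | Residual SD | Variance cut | Power, one test at 5% | Power, Bonferroni pair | 95% CI half-width |
|---|---|---|---|---|---|
| 0 | 2.50 | 0% | 90.2% | 79.7% | 1.21 |
| 0.15 | 2.47 | 2% | 90.8% | 80.8% | 1.20 |
| 0.2 | 2.45 | 4% | 91.3% | 81.6% | 1.19 |
| 0.3 | 2.38 | 9% | 92.6% | 83.9% | 1.15 |
| 0.5 (for contrast) | 2.17 | 25% | 96.3% | 90.9% | 1.05 |

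At r = 0.3 the gain is worth 34/(1 − 0.09) − 34 = 3.4 women per arm. At r = 0.15 it is worth 34/(1 − 0.0225) − 34 = 0.8.

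**The case against.** The strongest reply is that nothing here is invalid. Randomisation makes the unadjusted comparison unbiased, the sample size was set with an SD that does not rely on covariates, and it reproduces. That stands, and it limits the point to efficiency.

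Three stronger readings are tempting, and the documents do not support them:

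- **Every woman has a baseline value of the primary outcome.** Entry is by a follicle count or an oocyte count. A woman admitted by the follicle route need not have had a retrieval. What every woman has is a response classification.
- **Baseline FSH is also data already held.** FSH level is only an example, in a paragraph covering baseline and outcome data together. Nothing shown says that it is measured before randomisation, or in every woman, and the case report form is not reproduced.
- **The gain is large.** A correlation of 0.5 would lift Bonferroni-pair power to about 91%. Given the truncation, that would require a between-cycle correlation above 0.7 before restriction. The documents offer no support for such a figure.

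It can also be said that Step 4 already allows adjustment for unbalanced prognostic factors, and does not limit this to the minimisation factors. That is true and helps with chance imbalance. But such adjustment is conditional on what is observed, is secondary, and yields to the unadjusted result, so it does not recover the precision for the primary comparison.

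**Conclusion.** The point holds as a low-severity matter of efficiency. The article fixes an unadjusted primary comparison and so sets aside an entry variable that could tighten it. For an assumed correlation of 0.15 to 0.3, the cost is about 1 to 2 percentage points of power on a single two-arm test and about 1 to 4 points on a Bonferroni pair. On the confidence interval half-width it is 0.01 to 0.06 of an oocyte, against a target difference of 2. The size rests on the assumed correlation and the normal approximation. The omission itself rests on the text alone. It introduces no bias and does not undermine the 34 per arm.

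**What to change.** Amend Step 4 so that the primary oocyte-count model includes previous-cycle response as a pre-specified covariate, whatever balance is observed. Code it as a category so that women without an earlier retrieval have a value: no retrieval after inadequate follicles; retrieval with 0–1 oocytes; with 2; with 3 or more. Report the adjusted pairwise estimates with 95% confidence intervals as primary and the unadjusted ones as supportive, and reverse the precedence rule accordingly. Add FSH level only if the case report form shows that it is recorded before randomisation in essentially all women.

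The cost is a change of wording and a simple coding rule. Prior response is already collected to confirm eligibility, so no extra women, visits or tests are needed. Four categories use 3 of about 99 residual degrees of freedom (102 − 3).

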### Exclusion Criteria

• Women aged over 40 years.

• Women with a single ovary.

### Randomisation

Third party, distant, internet-based block randomisation with minimisation will be used to ensure randomisation and complete allocation concealment. The aim of minimisation would be to balance for the following prognostic variables (age, body mass index, previous pregnancies and previous live birth). Women may be randomised into the study by internet randomisation [12] or by telephoning a central office.

### Blinding

The trial will be a single-blinded study, where the assessors (the doctor performing the egg collection procedure and the embryologist involved in identifying and assessing the eggs) are blinded to the treatment regimen.

### Methods

All women who have had poor ovarian response in a previous IVF treatment cycle and who wish to undertake another IVF treatment cycle are invited to participate in the trial. The trial details are explained to the patient by a doctor at their clinic appointment. An information sheet [see Additional file 1] explaining the trial is given which also has a contact number to telephone and speak to the trial investigators. If the woman subsequently agrees to participate in the trial she is requested to sign a consent form [see Additional file 2]. The woman is then randomised to one of the three trial regimens and informed which regimen she has been randomised. Should the woman need more time to decide the clinic doctor will gain verbal permission for the investigators to call and ascertain whether the patient wishes to enrol on the trial. If the patient does wish to enrol then one of the investigators will make an appointment for the patient to sign the consent form. If the woman declines to participate then no further action is required with regard to the trial and the woman will receive standard care. The flowchart in figure 2 describes the participant flow in the trial. Details of all participants and outcomes are recorded on the case report form [see Additional file 3].

**Figure 2 F2:**
[figure not shown]
Participant flow chart through the PRINT trial.

### The treatment regimens

#### GnRH agonist long regimen (Figure 3)

**Figure 3 F3:**
[figure not shown]
GnRH agonist long regimen.

Pituitary down-regulation with GnRH agonist, nafarelin (Synarel; Pharmacia, UK) starts on day 21 of the menstrual cycle. Nafarelin nasal spray is taken at a dose of two sniffs, twice a day, where one sniff equals 200 micrograms. The woman will generally have menstruation within two weeks of starting nafarelin at which point she attends the assisted conception unit (ACU) for a transvaginal ultrasound scan (TVS) to confirm down regulation (quiescent ovaries with follicles < 10 mm diameter and endometrium < 5 mm in thickness). On confirmation of down regulation, ovarian stimulation is commenced with FSH, follitropin alfa (Gonal-F; Serono, UK) at 450 IU daily by subcutaneous injection. The dose of the nafarelin nasal spray is halved (one sniff, twice a day) during ovarian stimulation. The woman then attends for a TVS nine days after starting ovarian stimulation and is instructed to administer huaman chorionic gonadotrophin (HCG) subcutaneously when criteria for egg collection are met (see below). FSH and nafarelin are continued until HCG administration.

The approximate duration of this treatment regimen (ie from the start of nafarelin nasal spray, commenced on day 21 of the menstrual cycle, until the pregnancy test is performed) is 6 weeks.

#### GnRH agonist short regimen (Figure 4)

**Figure 4 F4:**
[figure not shown]
GnRH agonist short regimen.

Treatment for this protocol starts on day 2 or 3 of the menstrual cycle after a TVS has confirmed the ovaries are quiescent and the endometrium thin (<5 mm). The ovaries are generally quiescent and the endometrium thin at the beginning of a menstrual cycle. On the 2nd or 3rd day of the menstrual cycle the woman commences nafarelin nasal spray (one sniff twice a day, where each sniff equals 200 micrograms). This is continued until administration of the HCG injection (approximately 10 to 15 days from the start of nafarelin nasal spray). On the 3rd or 4th day of the menstrual

cycle the woman commences FSH (450 IU daily by subcutaneous injection). The woman attends for a TVS on day 9 of ovarian stimulation and is instructed to administer HCG when criteria for egg collection are met (see below). FSH and nafarelin are continued until the day of HCG administration.

The approximate duration of this treatment regimen (ie from the start of nafarelin nasal spray, commenced on day 2 or 3 of the menstrual cycle, until the pregnancy test is performed) is 4 weeks.

#### GnRH antagonist regimen (Figure 5)

**Figure 5 F5:**
[figure not shown]
GnRH antagonist regimen.

Treatment with this regimen starts on day 2 or 3 of the menstrual cycle. The woman will attend the ACU for a TVS and if the ovaries are quiescent and the endometrium thin (<5 mm) she will commence ovarian stimulation with a daily dose of 450 IU of FSH subcutaneously. Following this a TVS is performed on day 6 of ovarian stimulation to identify the leading follicle. Scans are continued until the leading follicle has a diameter of 14 mm which is usually between days 6 to day 8 of ovarian stimulation. When the leading follicle has reached a diameter of 14 mm, GnRH antagonist, cetrorelix (Cetrotide; Serono, UK) 0.25 mg daily is administered subcutaneously. The next TVS is performed on day 9 of ovarian stimulation, when the woman is instructed to administer HCG if criteria are met (see below). FSH and cetrorelix are continued until HCG administration.

The approximate duration of this treatment regimen (ie from the start of FSH injections, commenced on day 2 or 3 of the menstrual cycle, until the pregnancy test is performed) is 4 weeks.

The following steps of the treatment are the same for all the three treatment regimens.

### Criteria for HCG administration

When ≥ 3 follicles attain a mean diameter of ≥ 17 mm, HCG, choriogonadotrophin alfa injection (Ovitrelle; Serono, UK) 6,500 IU is administered subcutaneously.

### Egg collection (oocyte retrieval)

Egg collection is performed 34–38 hours after the HCG injection. Egg collection is routinely done under heavy sedation.

### Embryo transfer (replacement of embryos)

Embryo Transfer is performed two, three or five days following the day of egg collection, based on the number and quality of embryos available.

### Luteal support

All women undergoing IVF treatment are advised to self administer progesterone pessaries (Cyclogest; Alpharma, UK) 400 mg daily starting on the day of egg collection until the day of the pregnancy test, then until 8 weeks of pregnancy if the treatment is successful.

### Pregnancy test

All women are requested to do a home urinary pregnancy test 14 days from the day of egg collection.

### Early pregnancy scans

All women having IVF treatment have two early pregnancy scans at 6 and 8 weeks gestation.

### Trial statistics

#### Number of participants

Sample size calculation was based on the observed differences in eggs collected from existing literature as well as on the judgement on what constitutes as a clinically Minimally Important Difference (MID), which was judged to be increasing the number of oocytes retrieved from 3 to 5. For this difference of 2 oocytes retrieved, with a standard deviation of 2.5 (as observed in the existing literature), for a power of 90% and an alpha of 5%, 102 women in total will need to be recruited (34 each of the three arms of the trial).

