#### Step 2: Inter-group comparisons

A test for overall comparison (eg ANOVA, or if assumption for ANOVA are not met, a non-parametric equivalence such as Kruskal-Wallis) will be employed for each outcome across all three interventions (A, B, and C), and if this is found to be significant (at a p-value of ≤ 0.05), then we will proceed to pair-wise comparisons (i.e., A vs B, B vs C, A vs C). We appreciate that multitudes of pair-wise comparisons can suffer from Type I (false-positive) error, and will therefore adjust for multiplicity of comparisons (by using steps such as Bonferroni and Tukey's procedure).

The statistical procedures for pair-wise comparisons will depend on the nature of the data: for example, for dichotomous outcomes, we will use Fishers Exact Test or chi-square as appropriate, and for continuous outcomes we will use t-test if the observations in each trial arm are normally distributed; if non-normally distributed, then Mann-Whitney-U test will be employed. Although p-values will be reported, the focus will be on providing 95% confidence intervals around point estimates as these are more useful in interpreting the findings of the trial.

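### The stated 90% power is that of an unadjusted two-arm t-test; under the planned gated, multiplicity-adjusted analysis, 34 per arm gives about 79–82% for a given pair 2 oocytes apart

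*Protocol article*

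**What the plan says.** All references are to the protocol article.

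*Number of participants.* The minimally important difference is "judged to be increasing the number of oocytes retrieved from 3 to 5", the SD is taken as 2.5 from the literature, and the section concludes that "for a power of 90% and an alpha of 5%, 102 women in total will need to be recruited", that is, 34 in each of three arms. It names no test and no sidedness. It does not say whether the power refers to the overall comparison, to one pair or to all pairs, and it mentions no multiplicity adjustment.

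*Step 2: Inter-group comparisons.* Every outcome first gets an overall test across the three regimens (ANOVA or a non-parametric counterpart). Then, "if this is found to be significant (at a p-value of ≤ 0.05), then we will proceed to pair-wise comparisons". For the three pairs the authors "will therefore adjust for multiplicity of comparisons (by using steps such as Bonferroni", and Tukey's procedure is named alongside. The same section puts the interpretive weight on 95% confidence intervals.

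*Objective.* The trial is to establish which of the three regimens is the most effective.

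**The concern.** The two sections describe different tests. The sample size is that of a single comparison of two arms at a plain 5%. Step 2 never tests a pair that way: a pair has to pass a global gate and then a stricter threshold. Each hurdle costs power, and nothing in the sample size section pays for it.

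Power is the main quantitative claim of the design, and the Background justifies the trial by the need for an adequately powered three-arm comparison. If the figure for a given pair is about 80%, the chance of missing a true 2-oocyte difference in that pair is 18–21%, not the 10% a reader would take from the text. Naming one regimen as best on pairwise evidence is harder still.

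**Working it through.** **Inputs.** Difference 2 oocytes (3 versus 5), SD 2.5, alpha 5%, power 90%, 34 per arm: all from *Number of participants*. Gate at p ≤ 0.05, three pairs, Bonferroni or Tukey: from Step 2. Standardised difference: 2 / 2.5 = 0.8. Assumptions: SD 2.5 in every arm and normal-theory tests on means. The third arm's mean is not given, so it is placed at 3, 4 and 5 in turn.

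**Reproducing the plan's figure.** The sample size per arm for 90% power was solved for each candidate test:

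| Test | n per arm |
|---|---|
| Two-arm t-test, two-sided 5% | 33.8 → **34** |
| Two-arm t-test, one-sided 5% | 27.5 → 28 |
| Two-arm t-test, two-sided 0.05/3 (Bonferroni) | 43.7 → 44 |
| ANOVA, means 3/3/5 or 3/5/5 | 31 |
| ANOVA, means 3/4/5 | 41 |

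Only the first gives 34, and 3 × 34 = 102.

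**Power for one pair, before the gate.** The noncentrality is 0.8 × √(34/2) = 3.30.

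- Unadjusted 5%: critical value 1.997 on 66 df, power 90.2%.
- Bonferroni, 0.05/3 = 0.0167: critical value 2.457 on 66 df, power 79.7%.
- Tukey: critical value q/√2 = 2.379 on 99 df, power 81.9%.

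**Power of the overall test.** The noncentrality is 34 × Σ(mean − grand mean)² / 2.5², with critical F of 3.09 on 2 and 99 df.

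- 3/3/5 or 3/5/5: 34 × 2.667 / 6.25 = 14.5, power 92.9%.
- 3/4/5: 34 × 2 / 6.25 = 10.9, power 83.7%.

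**Gate and pairwise tests together** (200,000 simulated trials per configuration, normal data, 34 per arm):

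| Event | 3/3/5 | 3/4/5 | 3/5/5 |
|---|---|---|---|
| Overall test significant | 93% | 84% | 93% |
| Given pair 2 apart, gate + Bonferroni | 80% | 79% | 80% |
| Given pair 2 apart, gate + Tukey | 82% | 81% | 82% |
| Given pair 2 apart, gate + unadjusted 5% | 88% | 83% | 88% |
| At least one 2-oocyte difference found, Bonferroni | 91% | 79% | 91% |
| At least one 2-oocyte difference found, Tukey | 92% | 81% | 92% |

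Under 3/3/5, the best regimen beats both others in about 68% (Bonferroni) or 72% (Tukey) of trials, and in 83% with the gate and unadjusted pairs.

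**Familywise error.** With the gate and unadjusted 5% pairs, the simulated rate is 5.0% when all arms are equal and about 5% when two are equal and one differs. Adding Bonferroni takes the latter to about 1.7%. This is the closed testing principle: with three arms, a 5% global test followed by 5% pairwise tests already controls the familywise error.

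**The case against.** The strongest reply is that the text never says which hypothesis the 90% refers to. The first test of the primary outcome in Step 2 is the overall one. If one regimen differs by 2 oocytes and the other two are equal, that test has 93% power, and the chance of finding at least one true 2-oocyte difference is 91–92% even after adjustment. This stands. A reader might infer that the design falls short of 90% on every reading, and the figures do not support that. They support a shortfall for a given pair, and for every reading in the table when the third mean lies midway (79–84%), a configuration the document does not specify.

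Second, the adjustment methods are given only as examples, and an analysis plan may settle the choice. That is fair but does not rescue the figure. Both named methods give 79–82% per pair, and the gate with no further adjustment gives 83–88%.

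Third, a reader might infer that the second correction is a mistake. It is not. It is unnecessary for familywise control of the tests with three arms, but keeping it is a legitimate conservative choice. It also matches the emphasis on confidence intervals: Tukey intervals have simultaneous 95% coverage, whereas unadjusted pairwise intervals do not.

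Fourth, a reader might infer that the lower power would let a null result pass as evidence of equivalence. The protocol plans no equivalence claim and directs interpretation to confidence intervals. Likewise, the best regimen beating both others is one natural reading of the objective, not a decision rule that the protocol sets.

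**Conclusion.** The point holds for pairwise power. The 90% belongs to an unadjusted two-arm test that Step 2 does not perform. Under the analysis the plan commits to, power for a given pair 2 oocytes apart is about 79–80% with Bonferroni and 81–82% with Tukey, with little change whether the third mean is 3, 4 or 5. That is a loss of roughly 8 to 11 points from 90%. Type I error is protected and no estimate is biased, so this is a wrong statement of power, not a flaw that invalidates the analysis.

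The conclusion rests on SD 2.5 in every arm and on normal-theory tests of means. The negative binomial model proposed in Step 1 was not fitted; negative binomial data with the same means and SD, tested on group means, gave 78–81%. The two-arm t-test origin of 34 is inferred, because the text names no test, but the shortfall per pair does not depend on that inference. Losses and interim looks are not counted.

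**What to change.** **Main change.** Keep N at 102. In *Number of participants*, say which comparison the power refers to, and replace 90% with about 80–82% for a given pair 2 oocytes apart after the Step 2 adjustment. It would help to add the overall test's power (93% if two arms are equal, 84% if the third mean is midway) and the 68–72% for the best regimen beating both others under 3/3/5. This costs wording only, with no extra patients; the stated power becomes less favourable.

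**If 90% per pair is required.** About 44 per arm with Bonferroni: 3 × 44 = 132 women, 30 more than planned.

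**Optional.** Drop the second correction for the hypothesis tests, citing closed testing for three arms, and restate the power per pair as about 88% (3/3/5) or 83% (3/4/5). The cost is that unadjusted pairwise intervals lack simultaneous 95% coverage. Tukey intervals could be kept for estimation, with a note that an interval and its test may then occasionally disagree.
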